#### 11.5.4 ANALYSIS OF THE PRIMARY IMMUNOGENICITY ENDPOINT(S)

The primary immunogenicity endpoint will be measured as geometric mean titer (GMT) of anti-Vi IgG of Vi-DT (MD; Group A) and Vi-DT (SD; Group B) after 4 weeks of vaccination for equivalence comparison.

To assess the equivalence, the test between two different formulations on GMT of Vi-DT at 4 weeks will be performed with significance level of 0.05. The equivalence of anti-Vi GMT at 4 weeks post vaccination of Vi-DT between two different formulations will be analyzed using an analysis of covariance model with group and strata as covariates after log transformation. The equivalence of two formulations will be confirmed if the both limits of two-tailed 95% confidence interval of the ratio of GMT between two formulations of Vi-DT is within the equivalence margin of [0.67, 1.5].

---

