| Protocol Number: IVI T004                                                                                                                                                                                                                                                                                                                                                                                                                                                                                                                                                                                                                                                                           |                                  |
| Study Sites: Study participants may be enrolled from the following sites; 
 
• University of the Philippines Manila - National Institutes of Health, Ermita Manila
 
• Lingga Health Research Center Calamba, Laguna
 
• Putatan Research Center, Putatan, Muntinlupa City
 
• Magcase Health Center, San Pablo City, Laguna
 
                                                                                                                                                                                                                                                                                                    |                                  |
| Study Period (years/months)

Estimated date first participant enrolled: Jan 2020
Estimated date last participant enrolled: May 2020
Estimated duration of the trial: 18 months                                                                                                                                                                                                                                                                                                                                                                                                                                                                                                          | Phase of development: III |

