## 5.3 MEASURES TO MINIMIZE BIAS

### 5.3.1 RANDOMIZATION/MASKING PROCEDURES

The randomization list will be generated by an IVI independent statistician who is not directly involved in the study conduct. Eligible participants will be assigned to receive single dose of Vi-DT test vaccine (either from multidose or single dose formulation) or control vaccine in a (2.5) : (2.5) : 1 ratio (i.e. 750, 750, and 300 participants respectively). The randomization list will contain sequential numbers unique to each participant and the block randomization process will be employed to ensure an effective balance between the interventions.

Only the independent statistician will have a complete set of randomization lists. The individual site lists will be kept under lock and key by the pharmacy staff at all clinical sites. At the end of the study after unblinding of the participants, the lists will be returned to the statistician.

Two types of randomization list, one with randomization number only, and the second with randomization number and vaccine allocation will be prepared. Participants in the study will be randomized into three treatment groups within each age stratum: 6 to less than 24 months, 2 to less than 18 years, and 18 to 45 years. Randomization list “without the vaccine allocation” with numbers will only be shared with the blinded trial staff, for enrolling the trial participants and assigning them the randomization number. The randomization list “with the vaccine allocation” will be shared with the unblinded vaccine administrator (study nurse/pharmacist). If feasible, a web based randomization system may be provided to each site and in that case paper based randomization list will not be used.

Upon enrollment, in order to receive the study vaccine, participants will be sent to the vaccine administrator with their randomization number. The unblinded study nurse/pharmacist located in

a different room will administer vaccine(s) to the participant according to the randomization list. The randomization number of the participant receiving the study vaccine will be written on the empty vaccine vial and on the vaccine accountability log for record and reconciliation.

Trial staff other than the unblinded study staff will remain blinded to vaccine administration. The unblinded study nurse/pharmacist will not be involved in the evaluation of vaccine safety and will not discuss with the investigator and clinical staff about vaccines administered.

---

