## 11.5 DESCRIPTION OF STATISTICAL METHODS

### 11.5.1 GENERAL APPROACH

This study is a randomized, observer-blinded phase III study in healthy participants with age 6 months to 45 years old at the time of vaccination of investigational vaccine to assess the safety and the equivalence of immunogenicity of multi-dose formulation compared to single-dose formulation of Vi-DT in an adult participants (18 -45 year age stratum).

Unless specified as in section 11.3, for equivalence test, the significance level is 5% with two sided test.

Analysis of covariance will be used to adjust for baseline titers, stratification and imbalances in baseline characteristics if necessary.

Missing immunogenicity data will not be imputed for the analysis. If missing data is more than 10%, the analysis of missing pattern will be assessed and a multiple imputation technique will be utilized as a sensitivity analysis.

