#### 11.5.5 ANALYSIS OF THE SECONDARY IMMUNOGENICITY ENDPOINT(S)

The secondary immunogenicity endpoint will be measured as seroconversion rate of Vi-DT (MD) and Vi-DT (SD) after 4 weeks of vaccination for equivalence comparison.

For assessment of seroconversion rate, the proportion of participants with at least 4-fold rise anti-Vi IgG ELISA antibody titer at 4 weeks as compared to prior to the investigational product dosing (Day 0) will be calculated. The equivalence of anti-Vi seroconversion at 4 weeks post vaccination of Vi-DT between two different formulations will be analyzed using the generalized linear model for binomial distribution with group and covariates. The equivalence of two formulations will be confirmed if both limits of two-tailed 95% confidence interval of the difference of seroconvergence between two formulations of Vi-DT is within the equivalence margin of [-10%, 10%].

---

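### The only covariate in the primary GMT model is age strata, which is constant in the adults-only analysis; study site, by which randomisation lists appear to be held, is not named, so some precision may be lost.

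*Protocol*

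**What the plan says.** **Allocation (Protocol 5.3.1).** The method is blocked: "the block randomization process will be employed to ensure an effective balance between the interventions". On custody of the lists: "The individual site lists will be kept under lock and key by the pharmacy staff at all clinical sites". A replacement is allowed for: "If feasible, a web based randomization system may be provided to each site and in that case paper based randomization list will not be used". The only stratification factor named is age, in three strata: infants and toddlers under 2, children and adolescents under 18, and adults up to 45. No sentence says that site is a stratification factor or that blocks are nested in site. The Synopsis names four sites ("Study participants may be enrolled from the following sites").

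**Primary analysis (Protocol 11.5.4).** Log anti-Vi IgG at 4 weeks "will be analyzed using an analysis of covariance model with group and strata as covariates after log transformation". Equivalence needs both limits of the two-sided 95% CI for the GMT ratio to lie within [0.67, 1.5].

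**Secondary analysis (Protocol 11.5.5).** Seroconversion "will be analyzed using the generalized linear model for binomial distribution with group and covariates". The covariates are not listed.

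**General statement (Protocol 11.5.1).** "Analysis of covariance will be used to adjust for baseline titers, stratification and imbalances in baseline characteristics if necessary".

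**Population.** The Synopsis restricts the immunogenicity subpopulation to adults aged 18 to 45.

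**The concern.** The covariate written into the primary model does nothing. Every adult in the immunogenicity analysis belongs to the same age stratum, so the ANCOVA of 11.5.4, taken as written, is a two-group comparison of log titres. The one other factor on which allocation appears to be organised, site, is absent.

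If the blocks were built within site, the estimated MD minus SD difference is almost free of site effects by design. A model without site still counts the differences between sites as residual noise and so reports a standard error larger than the design produced. In an equivalence trial each increment of CI width counts directly against success, because both limits must clear the margins. What is at stake is power: a modest gain in precision given up.

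**Working it through.** **Inputs from the protocol (11.1, 11.3, 11.5.4).** CV 2.0; 250 adults per Vi-DT group; 10% dropout, taken as 225 evaluable per group; margins [0.67, 1.5]; two-sided 95% CI rule.

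**Assumptions.** Log-normal titres; true GMT ratio 1; arms balanced within site; a share ρ of log-titre variance lying between sites. The protocol does not give ρ, so a range is used.

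**1. Log-scale SD.** σ = √ln(1 + 2.0²) = √1.609 = 1.2686.

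**2. The plan's own figure.** SE = σ√(2/n). Power = Φ((ln 1.5 − z·SE)/SE) − Φ((ln 0.67 + z·SE)/SE), with ln 1.5 = 0.4055 and ln 0.67 = −0.4005.
- n = 250, z = 1.645 (a 90% CI): SE = 0.1135, power 94.3%. This reproduces the stated 94%.
- n = 225, z = 1.96 (the protocol's 95% CI rule after dropout): SE = 0.1196, power 84.1%.

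The gap between 94% and 84.1% is a separate matter. The second figure is used here only as the baseline under the stated decision rule.

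**3. Leaving site out.** With arms balanced within site, the estimate varies with SE_true = 0.1196·√(1 − ρ), but the model reports SE = 0.1196. The half-width stays at 1.96 × 0.1196 = 0.2344. Equivalence is declared if the estimate falls between −0.4005 + 0.2344 = −0.1660 and 0.4055 − 0.2344 = 0.1710, so power = Φ(0.1710/SE_true) − Φ(−0.1660/SE_true).

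**4. Putting site in.** Reported and true SE agree at 0.1196·√(1 − ρ), and the formula in step 2 applies with that value. The CI without site is wider by the factor 1/√(1 − ρ).

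| Assumed ρ | SE_true | Power without site | Power with site | CI without site is wider by |
|---|---|---|---|---|
| 0% | 0.1196 | 84.1% | 84.1% | 0% |
| 5% | 0.1166 | 85.2% | 86.5% | 2.6% |
| 10% | 0.1135 | 86.2% | 88.8% | 5.4% |
| 20% | 0.1070 | 88.5% | 92.9% | 11.8% |

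For example, at ρ = 10% without site: Φ(0.1710/0.1135) − Φ(−0.1660/0.1135) = Φ(1.507) − Φ(−1.463) = 0.862. The gains are 1.4 points at 5% and 2.6 points at 10%.

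**5. Simulation check.** Four nearly equal sites, MD:SD blocks of 10 within site, 225 per arm on average, 3,000 trials per value of ρ. CI-width ratios were 1.000, 1.019, 1.039 and 1.091 for ρ of 0, 5%, 10% and 20%. They are below the formula because drawing only four site effects realises on average three quarters of the nominal between-site variance; at ρ = 10%, √((0.90 + 0.075)/0.90) = 1.041. Simulated power without versus with site was 86.3% vs 87.2% at 5% and 86.8% vs 88.8% at 10%. Coverage of the unadjusted 95% CI was 95.6%, 95.7% and 96.4% at 5%, 10% and 20%, which confirms that the error is on the conservative side.

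**6. Cost in degrees of freedom.** Residual df fall from 450 − 2 = 448 to 450 − 5 = 445 with four sites.

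**The case against.** **Site blocking is inferred.** The sentence on site lists concerns who holds them. Age is the only stratum named, and a web system may replace the paper lists. This stands: separately held blocked lists make balance within site the natural reading, but the protocol does not state it. If the blocks are not nested in site, the model without site gives a correctly sized CI, not a conservative one, with power near 84.1% whatever ρ is. A site term would then still reduce the residual variance.

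**The protocol may already allow for site.** Section 11.5.1 provides for adjustment for stratification, 11.5.5 leaves its covariates open, and 11.2 defers further detail to an SAP that is not at hand. This stands in part, and the SAP may well include site. But 11.5.4 does not leave the primary covariates open: it names them, and the one it names is constant in this population. The wording in 11.5.1 is conditional and does not mention site.

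**Nothing planned is lost.** CV 2.0 describes total variability, so the model without site has at least 84.1% power at every site share. This is correct. The point is a gain not taken.

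**Lockdown effects.** A reader might infer that missed Visit 4 samples and the later extra adults leave the arms with different site mixes. The documents do not support that: the lockdown was external, the trial is observer-blind, and nothing suggests that losses differed by arm within site.

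**Conclusion.** The point holds as a low-cost improvement to a stated model. As written, the primary ANCOVA adjusts for no design factor: its strata term is constant in adults and site is not named. If sites differ and allocation was balanced within them, the 95% CI is conservative. With 5% to 10% of log-titre variance between sites, the CI is 2.6% to 5.4% wider than it need be and power is 1.4 to 2.6 points lower. With no site variance the loss is nil. These sizes rest on an assumed site share, log-normal titres with CV 2.0, 225 evaluable per arm and a true ratio of 1.

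A reader might infer that the primary conclusion is unsafe, or that the CI is certainly too wide. Neither follows. Leaving site out does not raise the risk of falsely declaring equivalence, and the excess width depends on a between-site variance that the protocol does not report.

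**What to change.** - **11.5.4:** replace the strata term with study site as a fixed effect in the model for log anti-Vi IgG, with small sites pooled by a rule set while blinded.
- **11.5.5:** name site as the adjustment factor for the seroconversion difference, for example through a site-stratified (Mantel-Haenszel type) risk difference with its 95% CI.
- **5.3.1:** state whether randomisation is stratified by site as well as by age, and whether that also holds under the web-based system.

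The cost is one model term, three short text changes and up to 3 of about 448 degrees of freedom. No new data or participants are needed.

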| Study Hypothesis

The scientific rationale described in this protocol, seeks to establish immune equivalence of a multi-dose formulation of Vi-DT (MD) compared to single dose formulation of Vi-DT (SD) in a subset of study participants of 18 to 45 years of age. The clinical research study is intended to assess immune equivalence for adult age stratum at 4 weeks post vaccination. The sample size calculation is based on the hypothesis of the immunogenicity endpoint which has been further increased to include safety data base from 6 months to less than 18 years age strata. Safety assessment of a single and multi-dose formulations of Vi-DT and control (Meningococcal |                                  |

conjugate vaccine) in age 6 months to 45 years will be evaluated by analyzing safety data descriptively at 4 and 24 weeks post injection.

In summary, safety population includes study participants from 6 months to 45 years old while the immunogenicity subpopulation is only in adults from 18 to 45 years of age.

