## 5 STUDY DESIGN

### 5.1 STUDY ENDPOINTS

#### Primary Endpoints

- Geometric Mean Titers (GMT) of anti-Vi IgG at 4 weeks (28 days) after vaccination of Vi-DT(MD)/ Vi-DT (SD) [18-45 year age stratum]

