### 11.5.2 BASELINE DESCRIPTIVE STATISTICS

Demographic characteristics and other baseline data of participants enrolled will be tabulated by vaccine group and overall. Continuous variables such as age, height and weight will be summarized by number of participants, mean, standard deviation, median, minimum and maximum. Categorical variables such as sex will be summarized by frequency and percentage in each vaccine. If a difference in baseline characteristics among groups is suspected, the statistical significance will be compared using ANOVA for continuous variables, and Chi-square test or Fisher's exact test for categorical variables.

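### The primary ANCOVA adjusts for strata that are constant in the adult-only analysis and leaves out the Day 0 titre; sections 11.5.1 and 11.5.4 need to be aligned on one model

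*Protocol*

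**What the plan says.** - **Primary model.** Protocol section 11.5.4 prescribes an "analysis of covariance model with group and strata as covariates after log transformation". Baseline titre is not among the terms.
- **Population.** The primary endpoint in section 5.1 is the week 4 GMT "after vaccination of Vi-DT(MD)/ Vi-DT (SD) [18-45 year age stratum"]. The Synopsis confirms that "the immunogenicity subpopulation is only in adults from 18 to 45 years of age".
- **Strata.** Section 5.3.1 says: "Participants in the study will be randomized into three treatment groups within each age stratum". Sections 4 and 11.1 name the same three age bands. Section 5.3.1 also mentions lists held by site ("The individual site lists will be kept under lock and key"), but nowhere calls site a stratum.
- **Covariates in general.** Section 11.5.1 says: "Analysis of covariance will be used to adjust for baseline titers, stratification and imbalances in baseline characteristics if necessary". No criterion for necessity is given.
- **Baseline tests.** Section 11.5.2 provides significance tests "If a difference in baseline characteristics among groups is suspected".
- **Data available.** Under section 5.2 and the schedule of events, adults give blood before vaccination and at week 4.
- **Timing.** Section 11.2 places a primary analysis after the week 4 visits and says that the SAP will be final before database lock. The lock described in section 5.3.3 is the one at 24 weeks.

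**The concern.** A covariate that takes one value for everyone cannot be estimated. As written, the prescribed ANCOVA adjusts for nothing. The one measurement likely to be prognostic for the Day 28 titre is each adult's own Day 0 titre. It is collected anyway, because seroconversion needs it, yet section 11.5.4 does not use it.

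Section 11.5.1 does not settle the matter, because its sentence can be read in two ways:

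- If the closing qualifier covers the whole list, baseline adjustment is discretionary and has no criterion.
- If it covers only the imbalances, baseline adjustment is required, and 11.5.4 contradicts it by leaving it out.

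On either reading the protocol does not state one usable primary model. At stake are the width of the interval that decides equivalence and certainty about which GMT ratio is the primary result. Precision matters here: section 5.2 (age strata reassignment) moves enrolment into the adult stratum to protect the power of this very test after lockdown prevented post-dose sampling.

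**Working it through.** **1. Levels of the strata term.** The named strata are 6 months to under 2 years, 2 to under 18 years, and 18 to 45 years. The primary analysis uses the third only: one level, zero degrees of freedom. The model reduces to log titre on group. Deleting the term changes no result.

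**2. Inputs** (protocol sections 11.1, 11.3 and 11.5.4)

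- CV 2.0, so the SD of ln titre is √ln(1 + 2²) = √ln 5 = 1.2686
- Margin 0.67 to 1.5: ln 1.5 = 0.4055, −ln 0.67 = 0.4005
- 250 adults per Vi-DT arm, and 250 × 0.9 = 225 after 10% dropout
- Decision by two-tailed 95% confidence interval, which is 0.025 per side
- Assumption: true GMT ratio of 1

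**3. Formula** (normal approximation)

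SE = SD × √(2/n); power = Φ(0.4055/SE − z) + Φ(0.4005/SE − z) − 1

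**4. The protocol's own figure.** With n = 250 and 0.05 per side (z = 1.645), SE = 0.1135 and power = Φ(1.928) + Φ(1.885) − 1 = 94.3%. This reproduces the stated 94%, but with every enrolled adult evaluable and a 90% interval.

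**5. Unadjusted power under the stated rule and dropout.** With n = 225 and z = 1.96, SE = 0.1196 and power = Φ(1.430) + Φ(1.388) − 1 = 84.1%. The t distribution gives 83.9%. The gap from 94% is a separate matter, used here only as the starting point.

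**6. Adding log Day 0 titre.** If ρ is the within-arm correlation of log Day 0 and log Day 28 titres, the residual SD is 1.2686 × √(1 − ρ²). The protocol gives no ρ, so a range is shown, with n = 225 and the 95% interval.

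| Assumed ρ | Residual SD | Power | CI multiplier on the ratio, exp(1.96 × SE) | Equivalent sample size, 1/(1 − ρ²) |
|---|---|---|---|---|
| 0 | 1.269 | 84.1% | 1.264 | 1.00 |
| 0.1 | 1.262 | 84.6% | 1.263 | 1.01 |
| 0.2 | 1.243 | 86.1% | 1.258 | 1.04 |
| 0.3 | 1.210 | 88.4% | 1.251 | 1.10 |
| 0.4 | 1.163 | 91.4% | 1.240 | 1.19 |
| 0.5 | 1.099 | 94.6% | 1.225 | 1.33 |

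The t-based powers are 0.1 to 0.2 points lower (84.4%, 85.9%, 88.2%, 91.2% and 94.5% for ρ from 0.1 to 0.5).

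**7. What an open model choice could do.** This was simulated at a true ratio of 1.5 with 225 per arm and 15,000 runs; the nominal error is 0.025.

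- Claiming equivalence if either the adjusted or the unadjusted analysis passes gives an error of about 0.027, 0.032 and 0.034 at ρ = 0.1, 0.3 and 0.5. As a cross-check, the two estimates have correlation √(1 − ρ²), so the error is 2 × 0.025 minus the bivariate normal probability that both pass: 0.027, 0.032 and 0.037.
- Adjusting only when a test of baseline imbalance has p < 0.10 gives about 0.024, 0.023 and 0.017. There is no inflation.

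**The case against.** The case on the other side is substantial.

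- **The redundant term is harmless.** It drops out and leaves a valid randomised comparison with no bias and correct error. This stands.
- **The loss of precision is not established.** It depends on a correlation that the protocol does not give, and at 0.1 it is about half a power point. This stands, so the gain can only be stated conditionally.
- **Baseline adjustment may already be intended.** This is a fair reading of section 11.5.1. On that reading 11.5.1 and 11.5.4 still disagree and must be reconciled.
- **Strata might mean site**, since lists are held by site. The protocol does not say so. This is a reason to name the terms, and to include site only if randomisation is stratified by it.

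A reader might infer that the sponsor can choose the model after seeing the results, with the tests in 11.5.2 as the trigger. The documents do not support that. Section 11.5.2 concerns baseline description and is not linked to the model, and the imbalance trigger simulated above did not inflate error. Nothing authorises reporting whichever analysis passes. Under sections 11.2 and 5.2 the SAP is to be final before database lock and data analysts stay blinded until the lock for the final analysis. That safeguard is incomplete, because the lock described comes at 24 weeks and the primary analysis follows week 4. Covariate detail may properly sit in a SAP, which is not at hand, but here the protocol itself fixes a model with an empty term.

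**Conclusion.** The point holds as a defect of specification with a possible, unquantified cost in precision. Section 11.5.4 prescribes an adjustment that does nothing in the analysed population, omits the Day 0 titre, and is not consistent with 11.5.1 on any reading that yields a definite rule. The comparison remains unbiased.

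Using the Day 0 titre would raise power from about 84% by about 0.5 point at a correlation of 0.1, 4 points at 0.3 and 10 points at 0.5. These figures assume a CV of 2.0, 225 evaluable adults per arm, a true ratio of 1, the 95% interval rule and a linear relation of log titres. It should be corrected because the change is free and the test is the trial's primary one. It does not invalidate the design.

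**What to change.** - In section 11.5.4, replace group and strata with group and log Day 0 anti-Vi titre, used whatever balance is observed. Add site only if randomisation is in fact stratified by site, and if so say so in section 5.3.1.
- In section 11.5.1, remove the conditional wording for this endpoint so that the two sections state the same model.
- State that the model is fixed before the week 4 data are unblinded, not merely before the 24-week lock.
- Report the unadjusted GMT ratio with its 95% interval as supportive.

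The cost is a few sentences in the protocol, repeated in the SAP. No new samples, visits or participants are needed.
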